### Phase 3: evaluation of the SAMAGH training Programme

SAMAGH will be evaluated through a process and outcome evaluation study as described in Fig. 3. Further description of the study design is presented in the next section.

**Fig. 3 Fig3:**
[figure not shown]
Description of the Process and Outcome Evaluation Study

#### Process evaluation

Health professionals who completed the training will take part in questionnaires and focus groups. The United Kingdom’s Medical Research Council (MRC) guidelines for evaluating complex interventions will be followed for the process evaluation [27]. Levels of adherence to the SAMAGH training programme will be assessed via the process evaluation.

All health professionals taking part in SAMAGH will be invited to take part in all three questionnaires (See Additional File 3). The pre-training questionnaire will measure health professionals’ current knowledge, attitudes and confidence relating to self-harm assessment and management, prior to attending the SAMAGH training. The baseline questionnaire to be conducted at the end of Day 2 of the SAMAGH simulation training, will measure: a) the acceptability of SAMAGH as an intervention to reduce hospital self-harm repetition rates and increase rates of mental health assessments being conducted with self-harm patients, b) gained knowledge on self-harm assessment and management. An online follow-up questionnaire will be conducted 12 months after receiving the training where the level of adherence to SAMAGH will be measured, as well as knowledge, attitudes and confidence on self-harm assessment and management. All questionnaires will be self-report, anonymous, and include a mix of true or false, open ended, multiple choice and Likert questions.

The sample of the focus groups will consist of 15 to 20 randomly selected health professionals attending the SAMAGH training programme. Randomisation of participants for the focus group will be done using a computer-randomised algorithm. Two focus groups will be conducted in total, approximately 3 months after the SAMAGH training, with 8–10 participants in each focus group. A topic guide will be used for the focus groups in order to obtain health professionals’ experiences supporting patients presenting with self-harm behaviour and existing challenges faced when offering support. Specific questions around observation of any changes for recurrence rates, and usefulness of the SAMAGH training programme will also be made. The focus groups will be conducted by specially trained researchers and will last approximately 2 h. Focus groups will be audio-recorded (if all participants agree to be recorded) and consent will be obtained for this data collection procedure. All participants will provide written informed consent prior taking part in the study.

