### Data management and access

The protocol complies with the Irish Data Protection Act of 1988 and the Irish Data Protection Amendment Act of 2003 and General Data Protection Regulation (2018). Only anonymised data will be released in aggregate form in academic journal articles, conference papers, and reports.

The Pre Training questionnaire and the 12-month online questionnaire will be conducted using the E-learning Website and Survey Monkey, which can be completed without providing any contact or personal information.

Existing protocols will be followed to ensure maintaining patient confidentiality. No details that would allow identification of participants will remain anywhere but in the consent forms, which will be securely stored.

The hard data from focus groups will be assigned ID numbers and the code key of participants’ names will be kept in a separate locked cabinet. Electronic data will be password-protected and stored on an encrypted computer within offices to which only NSRF staff have swipe access. Participants will be permitted access to their personal data at any time and will be entitled to withdraw their data from the study up to the point of publication. Manual data and electronic data will be stored securely in locked cabinets and encrypted computers within the NSRF offices for 10 years after collection.

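### The three trainee questionnaires are anonymous and no linking code is described, so within-person change and selective response at 12 months cannot be analysed in 40 to 50 people

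*Protocol article*

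**What the plan says.** Under Process evaluation, every trainee "will be invited to take part in all three questionnaires": before training, at the end of Day 2, and at 12 months. On content, "The pre-training questionnaire will measure health professionals’ current knowledge, attitudes and confidence relating to self-harm assessment and management". The end-of-Day-2 form covers acceptability and gained knowledge. For the last one, "An online follow-up questionnaire will be conducted 12 months after receiving the training", covering adherence and again knowledge, attitudes and confidence. The section closes with: "All questionnaires will be self-report, anonymous, and include a mix of true or false, open ended, multiple choice and Likert questions".

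Data management and access adds that the pre-training and 12-month forms are collected through the E-learning website and Survey Monkey, "which can be completed without providing any contact or personal information". It also says: "No details that would allow identification of participants will remain anywhere but in the consent forms". A linking device appears for one data source only: "The hard data from focus groups will be assigned ID numbers", with a code key held separately. None is described for the questionnaires.

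The third objective in the Aim section includes the effect of the training on professionals' knowledge, attitudes and skills. Phase 2 gives the number of trainees as 40 to 50, in about five groups of 8 to 10.

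**The concern.** An effect on knowledge, attitudes and confidence is a change within people, and the same people are asked before training and again at 12 months. If their forms carry nothing that joins them, two things are lost.

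- **The standard error of the change.** The within-person correlation cannot be estimated, so the analyst must treat the two sets as independent. With a positive correlation that makes the standard error too large and the test conservative, in a sample that is already small.
- **The check on selective response.** The 12-month form is online and a year later. If those who answer it already scored higher before training, the mean rises without any true change. The number of forms returned at each time will be known, but not whether the missing people differed at the start.

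A later analysis plan cannot repair this, because records collected without a key cannot be paired afterwards.

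**Working it through.** **Inputs from the protocol article.** 40 to 50 trainees (5 × 8 = 40, 5 × 10 = 50); three questionnaires, all anonymous; knowledge, attitudes and confidence measured before training and at 12 months. There is no questionnaire power calculation to reproduce. The only power statement (90% at 0.05) concerns the registry repetition rate.

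**Assumptions, none of them in the documents.** n = 45 respondents before training; m = 45 or 25 at 12 months, all of whom also answered before training; correlation ρ of 0.3, 0.5 or 0.7 between a person's two scores; equal SDs; two-sided 0.05; 80% power. Changes are in SD units.

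**Unlinked.** The two-sample test uses SE_used = √(1/n + 1/m). Because the same people answer, the true SE is SE_true = √(1/n + 1/m − 2ρ/n). The detectable change is about t × SE_used + 0.842 × SE_true, where t is the two-sided 5% critical value on n + m − 2 degrees of freedom.

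- n = m = 45: SE_used = √(2/45) = 0.211, t = 1.987.
  - ρ = 0.3: SE_true = 0.176; 0.419 + 0.148 = 0.57
  - ρ = 0.5: SE_true = 0.149; 0.419 + 0.125 = 0.54
  - ρ = 0.7: SE_true = 0.115; 0.419 + 0.097 = 0.52
- n = 45, m = 25: SE_used = √(1/45 + 1/25) = 0.249, t = 1.996.
  - ρ = 0.3: SE_true = 0.221; 0.498 + 0.186 = 0.68
  - ρ = 0.5: SE_true = 0.200; 0.498 + 0.168 = 0.67
  - ρ = 0.7: SE_true = 0.176; 0.498 + 0.148 = 0.65

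Simulating the two-sample t-test at the four ρ = 0.5 and 0.7 values and at the 45-then-25, ρ = 0.3 value gave power of 79% to 80%.

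**Linked.** Paired t-test on the m complete pairs, SE = √(2(1 − ρ)/m), power from the noncentral t distribution.

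| Respondents (before, 12 months) | ρ | Unlinked | Linked |
|---|---|---|---|
| 45, 45 | 0.3 | 0.57 | 0.51 |
| 45, 45 | 0.5 | 0.54 | 0.43 |
| 45, 45 | 0.7 | 0.52 | 0.33 |
| 45, 25 | 0.3 | 0.68 | 0.69 |
| 45, 25 | 0.5 | 0.67 | 0.58 |
| 45, 25 | 0.7 | 0.65 | 0.45 |

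In the 45-then-25 case at ρ = 0.3 the paired test is no better, because it drops the 20 people seen only before training.

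**Selective response.** Let r be the 12-month response proportion and g the pre-training difference, responders minus non-responders, in SD. With no true change, the unlinked comparison of 12-month responders with everyone before training shows (1 − r) × g. For g between 0.3 and 0.5 (assumed), that is 0.2 × 0.3 = 0.06 to 0.2 × 0.5 = 0.10 SD at 80% response, and 0.4 × 0.3 = 0.12 to 0.4 × 0.5 = 0.20 SD at 60% response. Linkage would allow g to be estimated; without it g is unknown.

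**The case against.** **The forms are not shown.** Anonymity does not exclude a self-generated code, which is neither contact nor personal information, and Additional File 3 might already contain one. This stands, so the point is limited to what the article describes.

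**This is a process evaluation, and the article plans no test on the questionnaires.** The statistical section covers two registry outcomes, and the questionnaire analysis may sit in a fuller plan. Leaving that analysis out is indeed no fault. But the third objective still asks for an effect, and the data structure that limits any such analysis is fixed here.

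**Anonymity protects candour.** Staff report their own attitudes and adherence in a programme whose facilitators include the national clinical lead. This is a fair reason to avoid names, but not to avoid a code that only the participant can regenerate.

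Three stronger readings are tempting, and the documents do not support them.

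- *That the design discards most of its precision.* With full response the mean change has the same sampling variance, 2(1 − ρ)/n, linked or not. What is lost is the ability to estimate that smaller standard error. Computing the unlinked case as if different people answered gives 0.60 SD for 45 and 45, and 0.71 SD for 45 and 25. Both are too pessimistic, since the same people answer.
- *That anonymity contradicts the right to withdraw.* Participants are "entitled to withdraw their data from the study up to the point of publication". That sentence stands in the paragraph on focus-group ID numbers and the code key, beside access to personal data, and reads naturally as covering identifiable records.
- *That all constructs have three time points, including skills.* Attitudes and confidence are listed only before training and at 12 months. Skills are not among the listed questionnaire constructs; simulation performance is graded separately by facilitators.

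**Conclusion.** The point holds for the questionnaires as the article describes them, and it should be acted on before the pre-training forms go out. Pairing is not possible with what is described, and the responder check is lost with it. Losing that check is the more serious of the two, because no assumption about correlation restores it.

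The loss in detectable change is moderate and depends on the assumed correlation and response. With full response from 45 people it is about 0.11 SD at correlation 0.5 and 0.19 SD at 0.7 (0.54 − 0.43 and 0.52 − 0.33). With 25 at follow-up it is about 0.09 and 0.20 SD (0.67 − 0.58 and 0.65 − 0.45), and nil for a simple paired test at 0.3. The point concerns the third objective only; the registry repetition and assessment rates do not depend on it. If Additional File 3 already carries a linking code, the article only needs to say so.

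**What to change.** Add one field to all three questionnaires for a code that each participant generates from fixed prompts, with no name or contact data. The description of the forms as anonymous can stay. The focus-group ID is not a substitute: it is described only for the 15 to 20 focus-group participants, about 3 months after training.

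Then state that:

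- change will be analysed with a paired or mixed model, using pre-training and 12 months for attitudes and confidence, and adding Day 2 for knowledge where the items match;
- a mixed model is preferred if 12-month response is incomplete, since it keeps people seen only before training;
- pre-training scores of 12-month responders and non-responders will be compared, with response counts at each time and the number of unmatched codes.

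The cost is one field on three forms and a sentence in the data management text. Some codes will not match, and a few participants may feel slightly less anonymous.

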#### Outcome evaluation

An outcome evaluation study will be conducted using a pre-post design. NSHRI aggregated data at a national level across the 27 hospitals in Ireland will be used, based on the 3 year average before the implementation of the SAMAGH training programme and 6 and 12 months after implementation of the programme. Outcomes to be included are: (a) hospital self-harm repetition rates, and (b) assessment rates following the hospital self-harm presentation. Aggregated data from the NSHRI allows for the analysis of hospital self-harm repetition rates of subgroups of self-harm patients, including patients with a history of 4 or more previous hospital self-harm episodes and those presenting to hospital following high-risk self-harm.

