**Methods/design:**

The study will be conducted in three phases. First, the SAMAGH Training Programme has been developed, which comprises two parts: 1) E-learning Programme and 2) Simulation Training. Second, SAMAGH will be delivered to healthcare professionals from general hospitals in Ireland. Third, an outcome and process evaluation will be conducted using a pre-post design. The outcome evaluation will be conducted using aggregated data from the National Self-Harm Registry Ireland (NSHRI) on self-harm repetition rates from all 27 public hospitals in Ireland. Aggregated data based on the 3-year average (2016, 2017, 2018) self-harm repetition rates prior to the implementation of the SAMAGH will be used as baseline data, and NSHRI data from 6 and 12 months after the implementation of SAMAGH will be used as follow-up. For the process evaluation, questionnaires and focus groups will be administered and conducted with healthcare professionals who completed the training.

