## Background

Self-harm and suicide are major public health concerns. Worldwide over 800,000 people die due to suicide every year and is the second leading cause of death among young people [1]. For each suicide, there are more than 20 suicide attempts [1]. In 2018, the National Self-Harm Registry of Ireland (NSHRI) recorded 12,588 hospital presentations due to self-harm nationally, involving 9785 individuals [2]. Compared to 2017, self-harm hospital presentations in Ireland have increased by 7%. Furthermore, over 22% of patients repeated self-harm. Similar increasing trends have followed worldwide [3], although certain decreasing rates have been reported [4]. Furthermore, there was a significant increase in certain highly lethal self-harm methods used, such as attempted hanging, which increased by 24% from 2017 [2]. Self-harm is one of the strongest risk factors for both non-fatal self-harm repetition and suicide, with evidence indicating certain groups being more prone to repeat self-harm and/or die by suicide (e.g. men, young people, older age groups, people engaging in more lethal self-harm methods and those with a history of 4 or more previous presentations) [5, 6].

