### Phase 2: implementation of the SAMAGH training Programme

An invitation to participate in SAMAGH will be sent to a representative group of 40 to 50 health professionals (Clinical Nurse Specialists, Non-Consultant Hospital Doctors, Psychiatry Registrars, Clinical Psychologists, Psychiatrists, among others) working across the 27 public hospitals in Ireland. Given that the SAMAGH Training Programme does not have a special focus on children, children’s hospitals will not be included in the recruitment of health professionals. Each group of health professionals will have representatives from a range of different hospitals across Ireland. Attending the SAMAGH training is not compulsory for health staff. SAMAGH will be delivered to groups of 8–10 participants, and there will be approximately five groups in total. It is expected that health professionals who complete the training will incorporate the learned skills and knowledge in their daily practice with self-harm patients.

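### A single flat 2016–2018 national average, with no comparator and no trend term, cannot separate the effect of training from background change; the hospital-level adjustment also does not fit national-level data

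*Protocol article*

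**What the plan says.** The first objective under Aim is causal: the effect of the training on repeated self-harm. The second asks whether training raises assessment rates.

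The Outcome evaluation section answers both with one design: "An outcome evaluation study will be conducted using a pre-post design". The data level is also fixed: "NSHRI aggregated data at a national level across the 27 hospitals in Ireland will be used". The periods to be compared are given there as "based on the 3 year average before the implementation of the SAMAGH training programme and 6 and 12 months after implementation of the programme". The Abstract names the baseline years: "Aggregated data based on the 3-year average (2016, 2017, 2018) self-harm repetition rates prior to the implementation of the SAMAGH will be used as baseline". It then sets the comparison period: "NSHRI data from 6 and 12 months after the implementation of SAMAGH will be used as follow-up".

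The Statistical analysis section compares baseline, 6 months and 12 months by Poisson regression with a moving window. It adds adjustment for service availability, hospital type and staff trained, among others. Calendar time, a pre-training slope and season are not named.

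Phase 2 describes an exposure likely to be uneven. Between 40 and 50 staff from across 27 hospitals are invited, in about five groups. "Attending the SAMAGH training is not compulsory for health staff", and children's "hospitals will not be included in the recruitment of health professionals".

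**The concern.** Averaging three years into one number leaves a single pre-training point. No slope can be estimated from one point, so the analysis cannot tell a training effect from a movement already under way. Nor is there a concurrent group to show what would have happened without training.

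The protocol gives reason to expect movement in this population. The Background states: "Compared to 2017, self-harm hospital presentations in Ireland have increased by 7" per cent. It also reports a 24% rise in attempted hanging over the same year. These are changes in volume and method, not in the repetition proportion, but they do not suggest a static background.

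At stake is the main conclusion on both registry outcomes. A background fall would be reported as benefit, and a background rise could hide a real one. The large registry sample makes this worse, because small national drifts become statistically significant.

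**Working it through.** **1. The plan's own figures (Sample size and power calculation; Background).**
- Person-based repetition, 2017: 1322/9103 = 14.5%, as stated.
- Act-based repetition, 2017: (11,600 − 9103)/11,600 = 21.5%, as stated.
- Power: 90% to detect 12% against 8% at 0.05. No sample size is given, so the 90% cannot be reproduced exactly. A two-sided two-proportion test needs 1181 individuals per period. With about 9103 a year, power exceeds 99.99%. Sampling error is therefore not the limiting problem.

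**2. Time gap.** The midpoint of 2016–2018 is mid-2017. Implementation follows the baseline, so a 12-month follow-up year starts no earlier than January 2019 and is centred no earlier than mid-2019. The gap is at least two years, and longer if training started later.

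**3. What the documents show about drift.** The act-based formula for 2018 gives (12,588 − 9785)/12,588 = 22.3%, a rise of 0.7 points in a year. Treating presentations as independent, z = (0.2227 − 0.2153)/√[0.219 × 0.781 × (1/11,600 + 1/12,588)] = 1.39. This is not significant and does not by itself prove a trend.

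**4. Smallest significant change.** Assumptions: three baseline years of 9103 individuals (27,309), one follow-up year of 9103, 14.5% repetition, independence.
- SE = √[0.145 × 0.855 × (1/27,309 + 1/9103)] = 0.426 points.
- 1.96 × 0.426 = about 0.84 points.

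**5. Chance of a significant result with zero training effect.** For a background fall d, let SE0 be the pooled and SE1 the unpooled standard error. Rejection probability = 1 − Φ[(1.96·SE0 − d)/SE1] + Φ[(−1.96·SE0 − d)/SE1].

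| Assumed background fall | Independent counts | Variance doubled |
|---|---|---|
| 0.5 points | 22% | 13% |
| 1.0 point | 66% | 39% |
| 1.5 points | 95% | 72% |
| 2.0 points | >99% | 93% |

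A fall of 1.0 point corresponds to an assumed 0.5 points a year over the two-year gap.

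**6. Random yearly variation without a trend.** With an assumed between-year SD of s points, the true SD is √[0.426² + s²(1 + 1/3)]. This is 0.72 points for s = 0.5 and 1.23 for s = 1.0. The nominal 5% two-sided test then rejects 24% and 50% of the time, half of it (12% and 25%) in the direction of benefit.

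**7. Data level against adjustment.** Hospital type and staff trained vary between hospitals. A national aggregate has one value per period, with no between-hospital contrast from which to estimate their effects. Either the model uses hospital-level data, contrary to Outcome evaluation, or the adjustment in Statistical analysis cannot be made.

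**The case against.** - **The design is openly declared, and trend terms may be in an unseen analysis plan.** Pre-post comparison is a legitimate description of change. But the flat average and the national level are stated choices, and a trend term added later has nothing to work on while the baseline is one number.
- **Exposure is not ignored.** This stands. Staff trained is listed for adjustment and, with hospital-level data, could give a dose contrast. What remains is that it is unspecified and does not fit the stated data level.
- **Untrained hospitals.** A reader might infer that the registry already contains untrained hospitals to serve as controls. The protocol identifies none. With 40–50 staff over 27 hospitals (1.5–1.9 each), random placement would leave about 4–6 without trained staff, but that is an assumption. Children's hospitals are outside recruitment because the programme has no special focus on children. They would be poor comparators, and the protocol does not say whether they are among the 27.
- **Drift is not demonstrated.** A reader might take the 7% rise, or the step from 21.5% to 22.3%, as proof that repetition was trending. The first concerns volume. The second is one non-significant step on the act-based measure, whereas the illustration uses the person-based 14.5%. Its direction is upward, which would mask benefit rather than create it.
- **The planned effect is large.** Even with a true SD of 1.23 points, a 4-point fall is about 3.2 SD. It would therefore be too strong to say that the analysis can support no conclusion at all. But the test declares success far below 4 points.
- **Season.** A full follow-up year balances season; the problem chiefly concerns the 6-month comparison.

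**Conclusion.** The concern holds in this form. Followed exactly, the plan estimates how national rates changed between about mid-2017 and a period at least two years later, and would present that as the impact of training. A background fall of 1.0 point alone would give a significant result about 66% of the time, or 39% with doubled variance. These figures rest on assumed counts, 14.5% repetition, and a drift whose size and direction the documents do not establish. The protocol gives no assessment-rate figures, so the same bias cannot be sized for that outcome.

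A fall as large as the planned 4 points would still stand out from drift of the sizes illustrated. Small and moderate changes could not be attributed to training. Separately, the national data level and the hospital-level adjustment are inconsistent as written.

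**What to change.** 1. Replace the three-year average with registry counts per hospital from January 2016, quarterly, or monthly where counts allow. At 9103 individuals a year, a hospital-month averages 9103/(27 × 12) = 28 individuals and about 4 repeaters. A hospital-quarter averages about 84 and 12. The subgroups will be sparser.
2. Fit a segmented Poisson model, allowing for overdispersion, with a pre-training trend, season, and a change in level and slope at training.
3. Use each hospital's number of staff trained and training date as the exposure contrast, and amend Outcome evaluation so that the data level matches the adjustment in Statistical analysis.
4. If some hospitals have no trained staff, or none yet, compare against them as a supporting analysis. It should not be the primary contrast until such hospitals are shown to exist. For illustration, with the counts in step 4 of the working and 50% to 85% of patients in hospitals with trained staff, a difference-in-differences has an SE of 0.85 to 1.19 points. Its power for a 4-point effect is 99.7% to 91.8%, before clustering, which would lower it.
5. Report the simple national pre-post change as descriptive.

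The cost is a finer registry extract, whose availability must be confirmed, more analysis work and wider confidence intervals. No new patient data collection is needed. Self-selection of hospitals and staff remains and should be stated as a limitation.
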